#### Qualitative assessment

Besides the quantitative assessment of data, a qualitative approach will be pursued. Therefore, the study team will conduct guideline-based telephone interviews with 10 relatives overall participating in the intervention group before and right after the implemented intervention in order to retrace the efficacy of the Dia*Life* education program in depth. The interview will focus on relatives’ physical and psycho-social diabetes-related burdens. All interviews will be audio-taped and analyzed along content analysis [16].

### Randomization and blinding

Study centers in the form of practices specialized in diabetes will be sequentially allocated at a ratio of 1:1 and stratified by diabetes type to either the intervention or control group by randomization. The randomization sequence will be generated by the Centre of Clinical Studies at the University Hospital Jena. Given the need to assign an equal number of study centers randomly to the intervention or control group, a computer-based block randomization will be applied [17] using nQuery 7.0.

Given that the study team has to inform study centers if they are going to train relatives within or after the study, it is not possible to blind the study centers. After signing the cooperation contract, the study centers will be randomized and informed about group allocation. The study centers will subsequently receive recruitment material, consent forms for patients, and other materials (e.g. questionnaires) by postal mail. Materials do not vary between the intervention and control groups. Participants will not know their group affiliation at the time of recruitment, but will know about it after giving written consent. The statistician concerned with randomization and data analysis will not be involved in other study-related assignments. Allocation concealment will be ensured for statistical analyses. The research team will remain blinded to the results until data collection is completed.

### Primary outcomes

#### Participating relatives

Difference in knowledge about diabetes between relatives of the intervention and control groups was determined as the study’s primary endpoint. Participants will be asked to answer knowledge-based questions before and after intervention (intervention group) or during regular consultation and care (control group). Result examination focuses on the question regarding if and to what extent knowledge has increased after the implemented intervention. Therefore, two questionnaires assessing relatives’ knowledge about diabetes type 1 or type 2 will be applied. These questionnaires will be developed following the templates used by Kronsbein et al. [18], that have already been applied by Pieber et al. [12]. Both questionnaires will consist of 16 questions regarding, for example, the impact of insulin on blood glucose, symptoms, causes and treatment of hypoglycemia and hyperglycemia, diabetes-related comorbidities, blood glucose monitoring, and impact of certain foods on the blood glucose level. In addition, the questionnaire for relatives of patients suffering from diabetes type 1 includes questions about glucagon shots, symptoms and treatment of ketoacidosis, and carbohydrate units. Relatives of patients with diabetes type 2 are additionally asked about the impact of certain factors (e.g. eating behavior) on blood glucose and what kind of preventive medical checkups are generally advised. The questionnaires used are available upon request from the authors. A translated version of the questionnaire is available in Additional files 2 and 3.

#### Participating patients

As the primary outcome, the current Hba1c value of participating patients will be assessed. Since Hba1c value assessment is mandatory once a quarter, it is not necessary to have it measured again for the study. The CDE will look up the latest Hba1c value from the patients’ case file and will document it.

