Relatives of the intervention group will complete the Dia*Life* education program in the version for the patient’s diabetes type. The group size for the educational intervention is set to a minimum of three relatives and to a maximum of six. Within the study, every mandatory and elective module will be taught by the CDE in their medical practice. It is intended to teach one Dia*Life* module per week, which means that the whole education program would take 8 or 9 weeks, respectively. However, since CDEs are challenged by a heavy workload, they can freely choose how many modules to schedule per week, but will be asked to complete the whole program in a maximum of 9 weeks. Relatives of patients with type 1 diabetes will attend nine modules overall, which are equivalent to an attendance time of at least 13.5 h up to 18 h. The program for relatives of patients with diabetes type 2 contains eight modules. Thus, the required attendance time is estimated at least 12 h up to 16 h. After recruitment, participating relatives will receive a schedule with course dates from their study center. The educational intervention will consist of lectures given by the CDE as well as (group) tasks, exercises, and discussions, which are all explained in detail in the trainer manual. Additionally, after completion of a module, participants will receive handouts with a summary of the most important topic-related information. After completing the educational intervention, the participants are expected to have extended diabetes-related knowledge, coping strategies, and improved communication skills. Furthermore, the education program should empower relatives regarding diabetes care.

In contrast, participating relatives of the control group will not attend the Dia*Life* program during the study, but will be assigned to a waiting list. As soon as the study is completed, participating relatives of the control group will be invited to attend the Dia*Life* education program. Consequently, all study participants will have the possibility to attend the education program regardless of group assignment, but at different points of time. Until relatives of the control group are invited to the Dia*Life* education program, they will receive no specialized training but will be involved in the management of the patient’s disease as before.

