#### Quantitative assessment

All relatives and patients will be asked to complete questionnaires at four different times, with baseline assessment at recruitment. Participants assigned to the intervention group will fill out a second questionnaire (follow-up 1) after completing the implemented intervention. Participants in the control group will also fill out a second questionnaire after an interval of approximately 8 weeks. In both groups, the second and third follow-ups will take place 6 and 12 months after follow-up 1, respectively. Parallel to all four moments of assessment, participating CDEs will be asked to complete a questionnaire for each patient in order to ascertain patients’ current health condition, their latest recorded Hba1c value, and their current diabetes treatment. Participants will be invited to all four assessments by postal reminder.

The data input will be performed successively. As soon as missing data are noticed, the study team will contact the corresponding CDE. The CDE will be asked to contact and remind the participants to provide missing data. The CDEs are also asked to report any drop-out as soon as it occurs.

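### The latest-on-file rule for HbA1c cannot give every patient a fresh value at follow-up 1, so any HbA1c contrast at that visit is diluted

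*Protocol article*

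**What the plan says.** Under Primary outcomes, Participating patients, the article makes the current HbA1c the patients' primary outcome and takes it from routine care: "Since Hba1c value assessment is mandatory once a quarter, it is not necessary to have it measured again for the study". The procedure is: "The CDE will look up the latest Hba1c value from the patients’ case file and will document it".

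Under Quantitative assessment, this applies at every visit: "Parallel to all four moments of assessment, participating CDEs will be asked to complete a questionnaire for each patient", covering among other things "their latest recorded Hba1c value". The first visit is fixed "with baseline assessment at recruitment". Follow-up 1 comes after the program in the intervention group. For controls: "Participants in the control group will also fill out a second questionnaire after an interval of approximately 8 weeks". Follow-ups 2 and 3 come 6 and 12 months after follow-up 1.

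Under Intervention scheme, the program is meant to take 8 weeks (type 2) or 9 weeks (type 1). Educators choose how many modules to hold per week but "will be asked to complete the whole program in a maximum of 9 weeks".

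The Primary endpoint paragraph under Data analysis gives a model with intervention fixed and center random, and names no visit. The Abstract describes 6 and 12 months as long-term efficacy and mentions regression models for effects over time.

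**The concern.** The reason given for not measuring HbA1c is that a routine value arrives each quarter. That works only where visits are at least a quarter apart. The first interval is shorter, so at follow-up 1 the latest value on file is, for some patients, the one already recorded at baseline. For most others it was drawn while the course was still running. Neither kind of value can show what the completed program did.

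At stake is how a follow-up 1 HbA1c result is read. A small or null difference there could not be told apart from an effect of the lookup rule. The share of repeated values can also differ by arm, because the interval from baseline to follow-up 1 is set differently in the two arms.

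**Working it through.** The article gives no figure for the share of fresh HbA1c values, so there is none to reproduce. Its sample size is built on relatives' knowledge and plays no part here.

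**Inputs**
- Q, weeks between draws: once a quarter (Primary outcomes, Participating patients), taken as 13, with 12 as a variant.
- L, weeks from baseline to follow-up 1: about 8 in controls (Quantitative assessment, reading the interval as running from the first questionnaire). In the intervention arm, 8 to 9 if the course starts at once and follow-up 1 falls at its end (Intervention scheme). The lag from recruitment to course start is not stated.
- g, weeks from program end to follow-up 1: not stated; 0 to 2 assumed.
- Draw dates: assumed to be spread evenly relative to recruitment.

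**1. Baseline value recorded again.** Share = max(0, 1 − L/Q).

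| Draw pattern | L = 8 | L = 9 |
|---|---|---|
| Every 13 weeks | 5/13 = 38.5% | 4/13 = 30.8% |
| Every 12 weeks | 4/12 = 33.3% | 3/12 = 25.0% |
| Interval varying around 13 weeks, SD 4 (simulated) | 40% | 33% |
| One random date per calendar quarter (simulated) | 42% | 36% |

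If patients are recruited at their quarterly visit and spacing is a strict 13 weeks, nobody has a new value at 8 or 9 weeks.

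**2. When new values are drawn.** With even spread, a new value falls uniformly between baseline and follow-up 1. Its mean time is L/2 = 4 to 4.5 weeks, about the middle of the program. The mean age of all file values is 13/2 = 6.5 weeks, which would suggest a draw in week 1.5 to 2.5. That average mixes in the repeated values already counted in step 1, so it does not describe the new ones.

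**3. Drawn after the program and by follow-up 1.** Share = g/Q: 0/13 = 0%, 1/13 = 7.7%, 2/13 = 15.4%. So about 85-100% of follow-up 1 values in the intervention arm pre-date the end of the program. A lag before the course starts does not change this.

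**4. Intervention arm if L is not 8 to 9 (Q = 13)**
- Lag giving L = 11: 2/13 = 15.4% repeated. L = 13: 0%. Under the calendar-quarter pattern these are 26% and 17%.
- Compressed course, two modules a week, L = 4.5 or 4: 8.5/13 = 65.4% or 9/13 = 69.2%.
- Controls stay at about 38% throughout, so the two arms can differ in either direction.

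**5. Later visits.** Follow-up 2 is about 26 weeks after follow-up 1. With 13-week spacing, the latest value was drawn at least 26 − 13 = 13 weeks after follow-up 1. For follow-up 3 the figure is 52 − 13 = 39 weeks. With one draw per calendar quarter, consecutive draws are less than 26 weeks apart, so a value drawn after follow-up 1 still exists at both visits.

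**The case against.** **No passage makes follow-up 1 the deciding HbA1c visit.** This stands. A reader might infer that it is, since 6 and 12 months are called long-term, and conclude that a null patient result would merely reflect the lookup rule. The documents do not support that. HbA1c is collected at all four visits, the model names no visit, and the before-and-after wording under Primary outcomes concerns relatives' knowledge. A condensed article may also leave the time point to the full protocol or analysis plan. What remains does not depend on the time point: a stated rule, followed as written, gives mostly pre-program or mid-program values at one of three follow-ups.

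**The educator's form is not shown and may already carry a draw date.** This stands too. One can say only that the article states no rule linking draw date to visit. A date field alone would not make the follow-up 1 values fresh.

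**The one-third figure is an assumption, and the arm that receives the program is the one whose interval is unknown.** This is correct, and it is why a range from about 0% to 69% is shown for that arm. It does not rescue follow-up 1, because a long lag reduces repeats without raising the share drawn after the program.

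**Repeated values in controls alone do not shrink a difference unless HbA1c drifts over time.** Agreed. The dilution comes from intervention-arm values drawn before the program is complete. Unequal staleness matters in addition only if there is such a drift.

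**Relatives' knowledge is what the article calls the study's primary endpoint, and two unaffected HbA1c visits are already scheduled.** This limits the reach of the problem and makes the repair easy.

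**Conclusion.** The point holds for follow-up 1 only. Assuming evenly spread quarterly draws and 8 to 9 weeks from baseline, about 31-38% of patients (25-42% across draw patterns) would have the baseline value recorded again. New values would be drawn on average around week 4 to 4.5, and only 0-15% after the program for a gap of 0 to 2 weeks. In the intervention arm the repeated share could run from about 0% to 65-69%, depending on the unstated lag and on how far the course is compressed, so it can differ from the controls' 38% or so.

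Any follow-up 1 HbA1c contrast is therefore diluted and cannot show the effect of the completed program. It does not follow that the patients' primary outcome as a whole is lost: the 6- and 12-month values are not affected in this way, and the article has not tied the primary HbA1c comparison to follow-up 1.

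**What to change.** 1. Name an existing later visit as the primary HbA1c time point, for example follow-up 2 at 6 months, and report follow-up 1 HbA1c descriptively.
2. Have the educator record the draw date with each value; for visits already held, retrieve it from the case file.
3. Apply the same window in both arms. The baseline value is the last one drawn on or before baseline. A follow-up 2 or 3 value counts only if it was drawn after follow-up 1 and within about one quarter of that visit.
4. Treat other values as missing, and add a sensitivity analysis that uses every file value regardless of date. This also guards against late-tested patients differing from the rest.

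**Cost.** One date field, one sentence on the time point, and a later read-out; no extra blood test. If the window looks back 13 weeks from the visit, strict 13-week testing loses no values. One random draw per calendar quarter would lose about 17% (the simulated share with no draw in a 13-week span), so the window length should be chosen with that in view.

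**Timing.** According to Trial status, enrolment ended in June 2019 and the protocol version is dated July 2019, so later visits were still ahead for late enrollees. The research team is to stay blinded to results until data collection ends, so these choices can be fixed before any result is seen.

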### Secondary outcomes

#### Participating relatives

Besides investigating differences and increase in knowledge, the study team defined additional outcomes such as differences in quality of life, family interaction, self-effectiveness, mental state, and perceived diabetes-related distress caused by the diabetes disease of a close relative.

Quality of life will be evaluated using the Short Form Health Questionnaire (SF-12) [19], which consists of 12 questions assessing the physical and mental health of participants. Furthermore, the Diabetes Family Behavior Checklist (DFBC) is applied to assess family interaction. The DFBC consists of 16 questions evaluating social interaction regarding patient’s diabetes management in daily life on a 5-point rating scale ranging from 0 (= never) to 5 (= always). Moreover, the DAWN Family Support Scale—Family Members (DFSS-FM) will be applied to assess familial support with seven items on a 5-point rating scale from 0 (= never) to 5 (= always) [20].

Additionally, relatives are asked to answer questions regarding distress caused by the diabetes disease. The questionnaire for relatives comprises two scales. The Problem Areas in Diabetes—DAWN Family Members Diabetes Distress (PAID-5-DFM) rates general distress related to the diabetes disease of a family member with a five-item battery on a 5-point rating scale (1 = no problem; 5 = major problem). To measure diabetes-related distress more accurately, the DAWN Impact of Diabetes Profile—Family Members (DDIP-FM) [20] is also implemented. Within the DDIP-FM, participating relatives are asked to rate the impact of the diabetes disease on certain areas of life, such as financial situation, emotional well-being, and occupation, using a 7-point rating scale (− 3 = strongly negative; 3 = strongly positive).

#### Participating patients

As secondary outcomes, diabetes-related distress, family interaction, and self-management will be assessed by implementing the scales presented in the following.

To assess diabetes-related distress of participating patients, they are asked to fill out inter alia the Problem Areas in Diabetes (PAID) scale [21]. The PAID assesses to what extend certain fields of diabetes management can be problematic (0 = no problem; 5 = major problem) with the help of 20 items on a 5-point rating scale. Family interaction will be assessed using an adapted version of the Diabetes Family Behavior Checklist Child Form (DFBC-C) [22], since a validated measurement of family interaction from the point of view of adult patients is missing. Additionally, the level of patients’ self-management will be determined by implementing the Diabetes Self-Management Questionnaire (DSMQ) [23]. Patients will therefore be asked to rate their diabetes self-management on a 4-point rating scale, ranging from 1 (= strongly agree) to 4 (= strongly disagree).

Moreover, in order to retrace feasible changes, the patients’ current diabetes medication will be gathered by the CDE with help of their case files.

### Other measures/covariates

In order to check for potential confounding effects, further data of both relatives and patients will be gathered. Signs of depression within the last 2 weeks will be assessed by implementing the German adaption of the Patient Health Questionnaire (PHQ-9) [24]. The PHQ-9 measures depressive symptomatology with a 4-point response scale from 1 (= not at all present) to 4 (= present almost every day). The severity of depressive symptomatology can then be classified into four categories (no depression, mild depression, pronounced depression, and severe depression) by calculating the sum score. Furthermore, the questionnaires ascertain sociodemographic variables of participating relatives and patients, such as educational attainment, level of income, and occupational status. Moreover, the CDE will document participants’ attendance at the course dates of intervention.

### Data collection and data management

Within the quantitative elicitation, data will be collected using questionnaires. Therefore, participants will be invited by postal mail to visit their respective study center in order to fill out the questionnaires. The study centers will then send the questionnaires back to the study team in a prepaid return envelope. To ensure high follow-up rates, participating relatives receive a monetary incentive of €50 after the completion of the last questionnaire. After every follow-up period, a trial manager will check whether data and study documents are complete. Data monitoring will be independent of the sponsor. Figure 2 shows the schedule of enrolment, interventions, and assessments according to recommendations for interventional trials (SPIRIT). A SPIRIT checklist is presented in Additional file 1.

**Fig. 2 Fig2:**
[figure not shown]
Schedule of enrolment, interventions, and assessments. DDIP-FM DAWN Impact of Diabetes Profile—Family Members, DFBC Diabetes Family Behavior Checklist, DFSS-FM DAWN Family Support Scale—Family Members, PAID-5-DFM Problem Areas in Diabetes—DAWN Family Members Diabetes Distress, SF-12 12-item Short Form Health Questionnaire

### Pilot study

Furthermore, two additional groups with six relatives of diabetes patients with DM type 1 or type 2, respectively, and with an immigrant background will attend the Dia*Life* program. However, we do not aim to investigate Dia*Life*’s efficacy in this small sample, but will assess whether the Dia*Life* education program will need any amendments to be applicable for people with an immigrant background. Therefore, the aim of this pilot study is to evaluate the comprehensibility of Dia*Life*’s curriculum and training material for relatives of patients with an immigrant background as a particular target group. Therefore, a pre–post survey without a control group will be conducted, in which also the type of cultural background will be assessed.

### Data analysis

#### Primary endpoint

A linear model with intervention as a fixed factor and study center as a random factor will be conducted. The estimated main difference between the intervention and control groups for a confidence level of 95% at a 5% significance level will be reported. Moreover, subanalyses of type 1 and type 2 participants are planned to assess Dia*Life*’s efficacy among relatives and patients with diabetes mellitus type 1 and type 2 independently.

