### Limitations

The evaluation study might be limited by using a cluster randomization of study centers instead of an individual randomization of participants. However, after careful consideration, the study team decided on a cluster randomized trial because of the practical implementation.

Relatives of patients with diabetes who have already participated in another education program for diabetes will not be excluded. Varying levels of diabetes-related knowledge and skills might affect Dia*Life*’s evaluation. However, since participating relatives’ state of knowledge will be evaluated in the baseline assessment, it is possible to control for this confounding variable in the analysis.

In addition, the Dia*Life* education program is designed for the healthcare situation in Germany and benefits from existing structures of diabetes care. However, these structures might be different in other countries. Thus, the Dia*Life* program might not be applicable elsewhere. Moreover, the curriculum of the Dia*Life* education program so far exists in German only, which might restrain non-native speakers from participation.

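### The stated primary model leaves out the baseline value and the diabetes-type stratum, which costs precision and protection against imbalance

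*Protocol article*

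**What the plan says.** Under Data analysis, Primary endpoint, the Protocol article states: "A linear model with intervention as a fixed factor and study center as a random factor will be conducted". It then says "The estimated main difference between the intervention and control groups for a confidence level of 95% at a 5% significance level will be reported", and adds "Moreover, subanalyses of type 1 and type 2 participants are planned". The headline result is therefore one difference pooled over both diabetes types. The Secondary endpoint paragraph uses the same two terms.

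Four other places bear on this:

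- **Primary outcomes, Participating relatives.** Knowledge is measured before and after, and the question is "if and to what extent knowledge has increased after the implemented intervention". There are two instruments, one per diabetes type: "Both questionnaires will consist of 16 questions regarding" a set of common topics. The type 1 version also covers glucagon, ketoacidosis and carbohydrate units; the type 2 version has additions of its own.
- **Quantitative assessment.** Questionnaires and the latest recorded HbA1c are collected at baseline and at three follow-ups.
- **Randomization and blinding.** Centers are allocated 1:1, "stratified by diabetes type to either the intervention or control group by randomization". They learn their arm before they receive the recruitment material.
- **Limitations.** On relatives who have already attended another diabetes course, the article answers that, because knowledge is measured at baseline, "it is possible to control for this confounding variable in the analysis".

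**The concern.** The article does name a model, and that model does not match what the rest of the text relies on. A limitation is answered by an adjustment that no stated analysis makes. A factor used to stratify the randomization is absent from the analysis. Scores from two different tests are combined with no term for which test was taken, and HbA1c is likewise combined across types.

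With about 16 centers, a chance difference between arms in prior knowledge is likely. Centers also recruit after learning their allocation, so baseline knowledge or type mix could differ by arm for reasons other than chance. Adjustment would deal only with the measured part of that; the crude model deals with none of it. At stake are the width of the confidence interval and how well the estimate stands up to a visible baseline difference. If the covariates are chosen only later, the analyst also has a choice that could easily be closed now.

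**Working it through.** **The plan's own figure.** From the Power calculation section: 12 per group; 12/0.9 = 13.3, rounded up to 14; design effect 1 + (11 - 1) x 0.21 = 3.1; 14 x 3.1 = 43.4, rounded up to 44. This reproduces, and nothing below changes it.

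**Inputs.**
- From the article: target difference 29 percentage points, 90% power, ICC 0.21, 11 relatives per center, at least 16 centers (8 per arm).
- Back-solved, because no SD is given: a two-sided 5% t-test with 12 per group and 90% power needs a standardized difference of 1.385, so SD = 29/1.385 = 20.9 points. A normal approximation gives 21.0-21.9.
- Assumed, because the article gives neither: the baseline-outcome correlation r, and the gap D in mean score between the two tests.

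**Step 1: precision from the baseline term.** Residual variance factor = 1 - r². This is an approximation applied to total variance, so it takes r to act alike between and within centers.

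| r | Variance factor | Variance reduction | Confidence interval narrower by |
|---|---|---|---|
| 0.3 | 0.91 | 9% | 5% |
| 0.5 | 0.75 | 25% | 13% |
| 0.7 | 0.51 | 49% | 29% |

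**Step 2: chance baseline difference between arms.** SD of the difference = SD x sqrt(2 x (ICC + (1 - ICC)/m)/k), for m relatives per center and k centers per arm.
- Pooled, m = 11, k = 8: ICC + (1 - ICC)/m = 0.21 + 0.79/11 = 0.2818, so 20.9 x sqrt(2 x 0.2818/8) = 5.5 points.
- Per type, centers recruiting both types, m = 5.5, k = 8: 20.9 x sqrt(2 x 0.3536/8) = 6.2 points.
- Per type, only if centers are single-type, m = 11, k = 4: 7.8 points.

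With equal SDs at baseline and follow-up, about r times the imbalance reaches the unadjusted estimate. A one-SD pooled imbalance of 5.5 points then shifts it by about 1.7, 2.8 or 3.9 points for r = 0.3, 0.5 or 0.7, which is 6%, 10% or 13% of the 29-point target.

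**Step 3: the type term.** Take a 50:50 type mix overall, so that omitting type adds D²/4 to the variance. The variance of a center mean is 20.9² x 0.2818 = 123.1.
- Centers recruiting both types, with type varying at random within a center: SE inflation = sqrt(1 + (D²/4)/(11 x 123.1)). D = 10 gives 1.009 and D = 15 gives 1.021, so 1-2%.
- Single-type centers: SE inflation = sqrt(1 + (D²/4)/123.1). D = 10 gives 1.10 and D = 15 gives 1.21, so 10-21%.

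The Recruitment of study centers section has every center recruit both types, so 1-2% is the figure for the design as described.

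**Step 4: effect on the pooled knowledge test.** With SE 5.5 and 14 degrees of freedom, power for 29 points is about 99.8%; with the SE raised by 21% it is about 98%.

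**The case against.** The strongest reply is that this is a condensed article and that the sentence gives only the design structure, treatment and cluster, without ruling out covariates. The outcome modelled might be a change score, since the endpoint asks about increase; baseline would then already be used, and a constant difference in difficulty between the tests would cancel. The abstract also promises hierarchical models for effects over time. This explains the brevity but does not remove the point. The Primary endpoint paragraph names no change score, baseline or time term. A change score would be less efficient than baseline adjustment and would still leave out the stratum.

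Several other objections stand:

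- The unadjusted mixed model is valid under randomization, and chance imbalance is already reflected in its standard error.
- Table 1 targets 44 relatives per type in each arm, so a type mix that differs by arm is hypothetical.
- The per-type subanalyses each use a single test.
- Both tests have 16 questions and the sample size works in percent correct, so pooling is not invalid in itself.
- On the plan's own inputs, the pooled knowledge comparison has ample power with or without adjustment.

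A reader might infer that the primary result would be biased, or that pooling the two tests makes it uninterpretable. The article supports neither.

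**Conclusion.** The point holds as a worthwhile improvement to a model the article states, not as a fatal flaw. The baseline term is the stronger part: it forgoes roughly 9% to 49% of residual variance for r between 0.3 and 0.7. It also leaves the estimate exposed to about r times any baseline imbalance, whose chance SD is about 5.5 points pooled. The type term belongs in the model because type is the stratification factor and defines which test is taken. Its numerical effect is about 1-2% on the standard error under the recruitment described; 10-21% would need single-type centers, which the recruitment section does not describe.

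These sizes rest on a back-solved SD and on assumed values of r and D. For HbA1c the article gives no SD or target difference, so the gain there cannot be sized. A reader might also take the Limitations sentence as a commitment to adjust; it says only that adjustment is possible.

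**What to change.** State the primary model as: post-intervention knowledge score = intervention + baseline knowledge score + diabetes type + random study center. Use the same form for HbA1c with baseline HbA1c, and carry it into the Secondary endpoint paragraph where a baseline value exists. Keep the model with intervention and center alone as a sensitivity analysis. Reword the Limitations sentence so that it refers to this adjustment as planned, and align the abstract's statement on effects over time with the analysis section. An intervention-by-type interaction is optional; it would support the subanalyses but is not needed to cure this defect.

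The cost is wording only. Every variable needed is already scheduled for collection and the sample size is untouched. The protocol version is dated July 2019, one month after participant recruitment closed, and the last follow-up comes 12 months after follow-up 1. At that date the change could be fixed before data collection was complete.
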